### Study aims

2.1

This clinical trial was conducted to confirm the clinical effectiveness and safety of KM treatment of unexplained infertility and to evaluate the cost-effectiveness relative to ART.

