### Design/setting

2.2

This study was designed as a multicenter, single-arm prospective clinical trial. All participants included will be from 3 hospitals: Dongguk University Ilsan Korean Medicine Hospital, Kangdong Kyunghee Korean Medicine Hospital, and Wonkwang University Kwangju Korean Medicine Hospital. Participants will be recruited through advertisements on bulletin boards at each medical center. The total target sample size is 100 subjects. All participants will voluntarily sign an informed consent agreement. Moreover, all participants will be enrolled after screening via the inclusion/exclusion criteria. All recruited patients will perform related surveys and tests, and be provided with treatments (herbal medicine, acupuncture, moxibustion). They will undergo an approximately 4 menstrual cycle treatment period and a 3 menstrual cycle observation period. If pregnancy occurs during the study, we will offer the herbal medicine to participants for about 15 days. The costs spent (transportation, time, care) in the previous treatment of the participants of this clinical trial will be investigated and compared with the conversion cost of this trial.

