#### Inclusion criteria

2.4.1

(1)Female over 20 and under 44 years of age;(2)Unexplained infertile female with a medical certification from a doctor of obstetrics-gynecology;(3)Has sexual intercourse more than twice a week.

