#### Primary outcome

2.6.1

The primary outcome of this study will be CPR. Clinical pregnancy was considered to be at least 1 gestational sac with fetal heart activity confirmed by ultrasound scan 5 to 6 weeks after pregnancy.^[18]^

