### Statistical analysis

2.8

The analysis set will comprise a full analysis set and a per-protocol set. Descriptive analyses including the mean, standard deviation, and frequency will be undertaken describing the baseline characteristics of participants. Continuous variables of primary and secondary outcomes will be presented in descriptive statistics and categorical data will be presented in frequency and percentage. When comparing and analyzing according to the level of specific variables such as demographic variables, continuous data will be tested using a Student's *t*-test or Wilcoxon's rank sum test. Categorical data will be analyzed using a chi-squared test or Fisher's exact test. For before and after comparisons, a paired *t*-test or Wilcoxon's signed rank test will be used. Repeated measures ANOVA will also be performed, whereas McNemar's test will be performed on categorical data. All statistical analyses will be conducted at a significance level of 0.05 and tested on both sides. Statistical analysis will be performed using the SAS program (version 9.4; SAS Institute Inc., Cary, NC).

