In this study, we will set up standard prescriptions according to the menstrual cycle on the basis of various studies and the prescriptions applied for infertility in Korea's representative large Korean medicine clinics. The standardized comprehensive treatment that can be applied to infertile women will be set up by combining herbal medicine, acupuncture and moxibustion. Overall, the ultimate purpose of this trial is to evaluate the effectiveness and safety of KM treatment for unexplained infertility and to evaluate the cost-effectiveness relative to ART. A total of 100 patients will be classified by age group, after which they will receive herbal medicine treatment according to patient's menstrual cycle and the CPR, IR, OPR, and live birth rate will be evaluated. To confirm the safety of KM treatment, we will check for adverse events every visit. Moreover, to evaluate cost-effectiveness, we will compare the economical effectiveness with that of ART.^[33]^

It should be noted that this trial has limitations. Specifically, it is based on a single treatment group without a blind, randomized control group. Because people usually do not want to wait to conceive, it is not easy to set up a control group. Therefore, literature pertaining to ART will be collected and used to replace a control group to compare the effectiveness and cost-effectiveness. This study is funded by the Ministry of Health and Welfare and the Korea Health Industry Development Institute and the results will be grounds for national policy projects. Moreover, to compare the effectiveness and economics of ART, the recruitment was based on the percentage of assisted reproductive costs supported in the country in 2010.

Despite these limitations, this clinical trial is the first to obtain an objective basis for the effectiveness and safety of KM treatment. The cost comparison with ART is expected to confirm the economic feasibility of Korean medicine treatment, which will allow us to offer a new direction in the treatment of infertility treatment, which is biased toward ART in Korea. We also expect it to be used globally as an alternative to solve the unexplained infertility.

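### The aim is to confirm that Korean medicine is effective, but the only external comparator is ART literature, which cannot separate treatment from spontaneous conception.

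*Protocol article*

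**What the plan says.** All places are in the protocol article.

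- **Aim (2.1 Study aims).** "This clinical trial was conducted to confirm the clinical effectiveness and safety of KM treatment of unexplained infertility", and to evaluate cost-effectiveness relative to ART.
- **Design (2.2 Design/setting).** "This study was designed as a multicenter, single-arm prospective clinical trial". Treatment lasts about 4 menstrual cycles and observation a further 3.
- **Primary outcome (2.6.1).** "The primary outcome of this study will be CPR". No reference value is attached, and the text does not say whether pregnancies count over the 4 treatment cycles or all 7.
- **Population (2.4).** Women with male, ovulatory, tubal, peritoneal or uterine factors are excluded, as are women planning insemination or IVF. Inclusion requires that the woman "Has sexual intercourse more than twice a week".
- **Comparator (3 Discussion).** The article concedes that "it is based on a single treatment group without a blind, randomized control group", explains that couples do not want to wait, and names the substitute: "literature pertaining to ART will be collected and used to replace a control group to compare the effectiveness and cost-effectiveness".
- **Use of the results (3 Discussion).** Despite these limitations, the trial is said to supply an objective basis for effectiveness and to inform national policy projects.
- **ART figures (1 Background).** CPR is about 33.5% for IVF and 10% for IUI. Whether these are per cycle or per woman is not stated.

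**The concern.** Women with no identified cause of infertility, regular intercourse and several further cycles of trying will sometimes conceive without any treatment. Whether KM works is a question about KM against no treatment. The plan names only ART as an outside reference, so it answers a different question: how KM compares with another active treatment in effect and cost.

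The limitation paragraph admits that there is no randomized control group, but it does not tell the reader that the observed CPR will include spontaneous conceptions. Nothing in the article allows that share to be judged.

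At stake is the main claim. An inert treatment could give a CPR close to the IUI figure and be described as comparable with IUI. The cost-effectiveness result would inherit the problem: if KM had no effect, comparing it with ART would in substance compare waiting with ART. The article expects policy to rest on these results.

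**Working it through.** **The plan's own figure.** The only sample size figure is N = 100. The age strata in 2.6.3 add up to it: 5 + 40 + 40 + 15 = 100. The article says N was set by the funding bodies rather than by the usual method, and it gives no null rate, target rate or power. There is nothing further to reproduce.

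**Inputs**
- n = 100 (2.2, 2.6.3)
- k = 4 treatment cycles, or 4 + 3 = 7 cycles in all (2.2); both are shown because the counting window is not stated
- IUI 10% and IVF 33.5% (1 Background)
- two-sided 0.05 (2.8), that is 0.025 in the upper tail
- untreated probability of clinical pregnancy per cycle, p: **not in the document**; assumed 1% to 5%, constant, with all women contributing every cycle

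**Step 1. CPR with no treatment effect:** CPR = 1 − (1 − p)^k. For example, at p = 2% and k = 7, 1 − 0.98^7 = 13.2%.

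**Step 2. Chance of at least 10 pregnancies in 100 women**, which would match the IUI figure: P(X ≥ 10), X ~ Binomial(100, CPR).

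| p per cycle | CPR, 4 cycles | CPR, 7 cycles | P(X ≥ 10), 4 cycles | P(X ≥ 10), 7 cycles |
|---|---|---|---|---|
| 1% | 3.9% | 6.8% | 0.6% | 14% |
| 1.5% | 5.9% | 10.0% | 7% | 55% |
| 2% | 7.8% | 13.2% | 25% | 86% |
| 3% | 11.5% | 19.2% | 72% | 99.6% |
| 4% | 15.1% | 24.9% | 95% | >99.9% |
| 5% | 18.5% | 30.2% | 99% | >99.9% |

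**Step 3. Untreated rate that reaches 10% by itself:** p = 1 − 0.9^(1/k). This is 1.49% per cycle over 7 cycles and 2.60% over 4.

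**Step 4. Stricter reading, significantly above the ART figure.** The smallest count whose exact upper tail is at most 0.025 is 17 of 100 against 10% (tail 0.021) and 44 of 100 against 33.5% (tail 0.018).
- At least 17, no treatment effect, 7 cycles: 0.04% at p = 1%, 16% at 2%, 75% at 3%, 99.9% at 5%.
- At least 17, 4 cycles: 0.2% at 2%, 6% at 3%, 69% at 5%.
- At least 44: at most 0.24% anywhere in the range (p = 5%, 7 cycles).

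**Step 5. Precision at n = 100.** The exact (Clopper-Pearson) 95% interval is 4.9% to 17.6% for 10 pregnancies and 11.8% to 28.1% for 19. Over 7 cycles, the interval for 10 pregnancies contains the no-effect CPR at p = 1% (6.8%) and at 2% (13.2%).

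**The case against.** **The design is deliberate and partly disclosed.** The article says there is no randomized control group, gives the reason and names the substitute. ART is the publicly funded option and a proper comparator for the cost-effectiveness aim. The Discussion also describes the purpose as evaluating effectiveness. All of this stands, but it does not supply an untreated reference, and the disclosure leaves out spontaneous conception.

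**Details may sit elsewhere.** How the CPR is tested against an external rate is commonly left to a statistical analysis plan, so the absence of a test in 2.8 is no finding. The choice of ART literature as the replacement for controls is different: the article itself fixes it.

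**The sizes rest on assumptions.** The untreated rate is assumed, the counting window is unstated, and 2.10 lets only women with at least 70% compliance continue, so not all will contribute every cycle. This is why a range and both windows are shown.

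**Two stronger readings are not supported.**
- Section 2.8 says McNemar's "test will be performed on categorical data". A reader might infer a before/after test of pregnancy, which could only favour treatment because nobody is pregnant at entry. But 2.8 presents categorical outcomes as frequency and percentage and does not assign McNemar's test to pregnancy. The laboratory tests in 2.9.1 are a natural source of before/after data.
- A reader might also infer that any CPR above a few percent could be reported as confirmed effectiveness. The stated comparison is with ART, and a few percent lies below both 10% and 33.5%.

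**Conclusion.** The point holds as a mismatch between claim and comparator. The aim is "to confirm the clinical effectiveness and safety of KM treatment of unexplained infertility", while the only external reference is another active treatment, so the plan cannot separate a KM effect from spontaneous conception.

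The exposure is mainly to a finding of comparability with IUI. Under the assumed 1% to 5% per cycle, an inert treatment would give a CPR of 3.9% to 18.5% over 4 cycles or 6.8% to 30.2% over 7. The chance of reaching 10 of 100 depends strongly on the rate and the window: from 0.6% (1%, 4 cycles) to near certainty (3% or more, 7 cycles). Significantly exceeding the IVF figure by spontaneous conception alone is very unlikely.

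These sizes assume a constant rate and complete follow-up. They also take the 10% at face value. If it is per IUI cycle, the cumulative equivalent is 1 − 0.9^4 = 34% over 4 cycles or 1 − 0.9^7 = 52% over 7, and a cumulative CPR set beside 10% would be on the wrong time base. That the results *will* be misread is a forecast; the documents show only that the plan has no safeguard against it.

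**What to change.** 1. **Widen the planned literature comparison** to expectant management in unexplained infertility. Use a range of rates matched on age and number of cycles, fixed before outcome data are seen. State the CPR counting window. Report the CPR in all enrolled women with an exact 95% interval beside that range.
2. **Limit the claim.** In 2.1, and in the matching wording of section 3, replace confirming effectiveness with estimating the CPR. Name spontaneous conception among the limitations. Treat a CPR above the benchmark as supportive evidence only: a literature rate is not a known constant, and this cohort is selected on intercourse frequency, prior IVF and KM diagnosis. Even a lower confidence limit above the benchmark would not establish effectiveness without a control group.
3. **Keep the ART comparison as a separate question** of relative effectiveness and cost.

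This needs no new arm and no change to treatment. The cost is a slightly wider literature search, some rewording and a weaker claim. Recruitment is described as ongoing, so all three steps can still be taken before outcomes are analysed.

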### Trial status

3.1

Patient recruitment is ongoing. Patient enrollment and trial completion is expected by May of 2018.
